## Study management

3

The Data Monitoring Committee (DMC) would consist of no less than two members of the Ethics Committee of the Luoyang First People’s Hospital. None of the members would have any conflict of interest regarding the research. The members would monitor the progress of the research study periodically and inform the Ethics Committee. They would not be involved in the research. In the case of unapproved changes to the research, the members of the DMC would recommend the termination of the research. Although AI-HEALS is a behavioral and mobile health–based intervention, similar mHealth or AI-assisted self-management programs have generally demonstrated a strong safety profile, with few or no serious adverse events (AEs) reported. Expected adverse events (if any) are expected to be minimal and non-physiological in nature, such as frustration when using technological devices, increased psychological burden caused by frequent reminders, or inconvenience during system interaction. No direct biomedical risks are expected, as the intervention does not involve pharmacologic, device-based, or invasive procedures. In the case of any AEs and serious AEs occurring to the participant, it would be communicated to the principal investigators within 24 h, and the study would be paused for further check. In case of major technical failure of the AI system and serious problems that might pose risks to the participants, as well as any issues regarding the user interface, the study would be halted immediately. Repairs would be conducted by the technical team. After the system had been repaired and stability had been confirmed, the study could either be reframed and continued if it was safe and sound scientifically.

Prior to the initiation of the study, system-oriented training and intensive assessments aided by subject matter experts will be carried out to ensure that all team members acquire broad knowledge of study procedures and technical finer points. To ensure minimal loss to follow-up, each participant will be properly registered as well as provided with a unique identification code. Additionally, to ensure convergence of the intervention as well as control arms, all assessments will be carried out at standard time points utilizing validated questionnaires. To permit data accuracy, a double data entry as well as validation system shall be instituted, thus enhancing data processing quality. After data analysis, the research team shall continuously engage statistical experts to determine the best data analytical methods suitable for the data at hand. If data processing gives detected irregularity or anomaly, the original questionnaires shall immediately be reviewed to determine data accuracy. Only data validated as accurate shall constitute part of the final analysis. These rigorous procedures serve to safeguard the validity as well as reliability of study results.

Regular supervision of the research team by the principle investigator shall ensure strict adherence to study protocol and complete acquisition of study data. If it becomes evident that data collection or follow-up procedures have not been conducted according to established protocols, appropriate corrective actions may be taken, such as terminating the trial or modifying the randomization schedule. Data collection shall only continue following implementation of the needed changes. In the event that systemic or widespread errors are found to exist in questionnaire design, or data recording errors found on conduct of the study, the research team shall place on hold conduct of the trial temporarily for correction and redesign of the instrument. Redesign of the questionnaire shall be accompanied by re-administration of the questionnaire to participants to obtain data that accurately reflect the study goals as well as desired outcomes of the study. These quality control steps are necessary to ensure the scientific rigor of the trial as well as adding to the reliability as well as validity of the results of the study. All of the data shall be handled by a data manager of design for that role. Data entry functions shall have a trial manager to watch over them, deal with cloud storage, as well as resolve issues that involve data management as well as accessibility of that data. The trial manager shall also carry out routine audits to ensure that data obtained are accurate, consistent, as well as adherence to the study protocol.

Unblinding shall only be permissible on exceptional grounds. Situations may involve emergency medical situations where knowledge of group assignment becomes unavoidable, such as when there arises a serious adverse event or when emergency treatment must be established. Participants or their doctors may similarly ask for unblinding after the conduct of the trial for legitimate medical reasons. Unblinding must always be requested through a written application submitted by means of the principal investigator or through a member of a clinical oversight team. All such requests shall pass through a clinical adjudication panel for determination as to whether there are grounds for unblinding. If granted, the participant’s assignment shall be revealed through established procedures, balancing participant protection and confidentiality.

All changes that are suggested to the study protocol will first be considered and reviewed by the Steering Committee. After consensus, the changes that are suggested will be sent to the hospital’s Ethics Committee and Research Administration Office for approval. Following approval, an official statement of changes will be distributed to all persons involved, with electronic copies as needed. All changes to the protocol will be signed by the principal investigator upon notification by the trial coordinator. The paperwork will be stored among other documents of the trial. Following approval by the Steering Committee, Research Administration Office, and Ethics Committee, the trial coordinator will make corresponding changes to the clinical trial registration.

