### Randomization and blinding

2.2

Single-blinding will be applied for the study, because the AI-HEALS intervention would not be possible for the participants and the intervention team to be blinded regarding the allocation of the groups. In the context, single-blinding indicates that the people involved in the evaluation process and analysis are blinded to the allocation groups of the participants during the evaluation and data analyses. For the randomization process, it would implement the use of the computer-generated random number sequence. For allocation, it would use the 1:1 allocation ratio. An independent team member who is not involved in participant recruitment, clinical care, or intervention delivery will generate the randomization sequence and manage allocation concealment. Group assignments will be released to the intervention team only after allocation is complete to ensure that recruitment personnel remain blind to group assignment at the time of enrollment. For avoiding sharing between allocation groups, the participants would be admitted to separate units according to their allocation (Ward A for the intervention and Ward B for the control groups). Although participants and care providers cannot be blinded, several measures will be implemented to reduce performance and detection bias:

Outcome data will be collected by research assistants who are blinded to group allocation.Data analysis will be performed by statisticians who are blinded to group identities, with datasets fully de-identified prior to analysis.Randomization and allocation procedures will be managed by an independent researcher not involved in recruitment or intervention provision.Physical separation of inpatient units will minimize interaction between participants from different groups.

All data will remain securely stored and de-identified to maintain the integrity of the blinding process.

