### Statistical analysis

2.11

Quantitative data will be gathered using structured questionnaires and would then be entered into Microsoft Excel for analysis. All major analyses would follow the intention-to-treat (ITT), and the per-protocol (PP) analysis would be performed for sensitivity testing. Descriptive statistics would be utilized for summarizing starting information, feasibility variables such as the number of participants, and use of the system.

For continuous data, the mean and standard deviation for normally distributed data, and the median and 25th to 75th percentiles for non-parametric data, will be presented. For comparison of groups initially untreated, and for groups measured once, independent samples t-tests and their non-parametric analogs would be employed. Categorical data would be expressed as frequency and percentage and would be analyzed using chi-squared tests. Normality of the data would be tested using the Kolmogorov Smirnov test.

Missing data will be handled using established multiple imputation methods where appropriate, under the assumption that data are missing at random. Patterns of missingness and attrition will be examined and compared between groups to identify potential differential dropout, and sensitivity analyses will be performed to compare imputed and complete-case results.

For the main trial, the focus would be on the use of the linear mixed-effects models for the evaluation of the primary outcome measures, such as the blood pressure, blood sugar, and blood fats. Additionally, the age factor would be incorporated as the covariate, which would account for the differences that people of varied ages would present, especially between the ages of 18 and 60. For secondary outcomes, such as the self-management and the psychosocial/cognitive outcomes, the analyses would use similar mixed-effects models or simpler comparative methods, depending on the nature and timing of the data collection. Also, exploratory age-stratified analyses may be conducted to descriptively examine potential heterogeneity of intervention effects across age groups, with results interpreted cautiously given the pilot nature of the study.

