Measures of system use (e.g., numbers of questions) will be summarized descriptively and may be included as covariates in exploratory analyses to better understand adherence patterns; these analyses will be considered hypothesis-generating rather than confirmatory. All statistical tests will be two-tailed with a significance level of 0.05. Data analyses will be performed using IBM SPSS Statistics (version 24.0; SPSS Inc., Chicago, IL, United States) and Stata (version 14.0; StataCorp, College Station, TX, United States).

At 3, 6, and 9 months following the completion of the intervention, this study will conduct structured interviews to assess participants’ perception of the intervention as attractive, acceptable, easy to use, and satisfactory as a whole. These interviews will attempt to identify, in depth, the most prominent determinants of behavior change and engagement. Each interview should be approximately 30 min long to conduct and may be conducted over the telephone or face-to-face. Participant recruitment will take into account socio-demographic variables like residence, gender, age, education level, as well as stroke severity, to attain diverse representation. Content of interview will include participants’ own experience of the intervention, suggestions for improvement of AI-HEALS system, motivation to pursue self-management activities, as well as challenges that develop in the process. To attain richness as well as data breadth, interviews should be continued until thematic saturation has been achieved. All interviews should be audio-recorded, transcribed verbatim, as well as de-identification carried out on them. Data analysis should make use of the Theoretical Domains Framework (TDF) on NVivo 12 (Version 12, QSR International, Doncaster, Australia). Lastly, qualitative findings would be integrated with quantitative data to attain a richer understanding of the impact of the intervention as well as long-term effects on participants’ health behavior as well as outcomes.

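### Study management allows the randomisation schedule to be changed after conduct lapses and, read literally, leaves the choice of analysis methods until after the data have been analysed

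*Protocol article*

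**What the plan says.** Two rules in section 3 (Study management) of the protocol article are at issue.

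The first concerns allocation. The trigger is a conduct failure: "If it becomes evident that data collection or follow-up procedures have not been conducted according to established protocols". The response is that "appropriate corrective actions may be taken, such as terminating the trial or modifying the randomization schedule", and data collection resumes once the changes are in place. The text does not say who would change the schedule or what limits apply.

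The second concerns analysis: "After data analysis, the research team shall continuously engage statistical experts to determine the best data analytical methods suitable for the data at hand".

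Three statements elsewhere bear on these rules:

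- Section 2.2 (Randomization and blinding) specifies a computer-generated sequence. On the ratio it says: "For allocation, it would use the 1:1 allocation ratio". The sequence and its concealment are given to an independent member with no part in recruitment, care or delivery of the intervention.
- Section 2.11 (Statistical analysis) names a model: "the focus would be on the use of the linear mixed-effects models for the evaluation of the primary outcome measures", with age as a covariate.
- Section 2.11 also sets the error level: "All statistical tests will be two-tailed with a significance level of 0.05".

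**The concern.** A missed visit or a badly recorded value happens after the participant has been allocated. Changing the list of future assignments does nothing to repair it. What the change can do is open a route by which knowledge gained after allocation (attrition, engagement, early results) shapes who is assigned to what next. Randomisation and an independently held sequence exist to close that route.

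The method rule raises a similar problem at the other end of the trial. A 0.05 test has a 5% false-positive rate only if the test was chosen without reference to its result. A rule that places the choice after the analysis, and ties it to the data in hand, removes that basis.

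Both are things the protocol states, so a separate analysis plan or a fuller protocol that is silent on them would not answer the point. The trial is also meant to supply effect and variability estimates for a larger trial (section 2.4), so any distortion would carry forward.

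**Working it through.** **Allocation rule.** No figure can be recomputed here, so the check compares the texts.

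1. The trigger lies in data collection or follow-up, and both come after allocation in Table 1.
2. The trigger can occur while assignments remain to be made. Enrolment runs from February 2025 to February 2026, about 12 months. The intervention lasts 3 months, with assessments 3, 6 and 9 months after it ends. For the first participants these fall about 3 (end of intervention), 6, 9 and 12 months after the start. Much of their follow-up therefore overlaps with recruitment.
3. Section 2.2 puts the sequence with an independent member. Section 3 neither repeats this nor requires that member to act when the schedule is changed.
4. Section 3 requires Steering Committee, Ethics Committee and Research Administration Office approval for changes to the protocol, and the monitoring committee acts on unapproved changes. A schedule change is already listed in the protocol as a permitted action, so it is unclear that either safeguard would be triggered.

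**Method rule.** The plan's own figure is the two-sided 0.05. With one analysis fixed in advance the rate is 1 − (1 − 0.05)^1 = 0.05, which reproduces it.

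If k analyses are all eligible and the smallest p-value is reported, independent tests give 1 − 0.95^k:

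- k = 2: 9.75%
- k = 4: 1 − 0.8145 = 18.5%
- k = 5: 22.6%

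Analyses of the same variable are strongly correlated, so the realistic inflation is smaller and was simulated.

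- From section 2.4: 25 per arm, and 30 per arm recruited.
- Assumed: normal data, no true effect, baseline-outcome correlation ρ of 0.3, 0.5 or 0.7.
- Outcome: y = ρ·baseline + √(1 − ρ²)·noise.
- Four analyses: t-test at follow-up, Mann-Whitney test, t-test on change, and a linear model adjusted for baseline and age.
- 6,000 simulated trials per setting. The Monte Carlo standard error near 10% is √(0.10 × 0.90 / 6000) = 0.4 percentage points.

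| Per arm | ρ | Smaller of t-test and Mann-Whitney below 0.05 | Smallest of four below 0.05 |
|---|---|---|---|
| 25 | 0.3 | 6.0% | 10.1% |
| 25 | 0.5 | 5.5% | 10.2% |
| 25 | 0.7 | 5.5% | 10.9% |
| 30 | 0.3 | 5.9% | 9.8% |
| 30 | 0.5 | 5.9% | 10.5% |
| 30 | 0.7 | 5.4% | 10.7% |

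Each of the four methods alone stayed between 4.3% and 5.3%. A separate run at 24 per arm (30 × 0.8, after the stated 20% dropout) gave 9.9%, 10.4% and 11.0% for the smallest of four. Adding a fifth option, the adjusted model on a subset with a random 20% removed (assumed, to mimic a per-protocol set), gave 11.2% to 12.4%. All rates are for one variable at one visit.

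**The case against.** The case on the other side is substantial, and parts of it stand.

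- **The wording is permissive.** The schedule change is one example of what may be done, and it may never be used. This stands: the rule can compromise randomisation but does not by itself break it.
- **The sequence holder is independent.** Nothing in section 3 takes control away from that person, and a revised list held there need not reveal coming assignments. This lowers the risk. It does not explain why a follow-up lapse should lead to a new list.
- **The timing phrase may be a slip.** Choosing methods after analysis is odd as a sequence of events, and before may have been meant. If so, the sentence still needs correcting, because staff work from the text.
- **The trial is a pilot.** Section 2.4 says it is not powered for hypothesis tests, which reduces the weight of the 5% argument. Section 2.11 still applies 0.05 to every test.
- **The 10-11% is constructed.** Section 2.11 does not offer the four simulated analyses as alternatives for the primary outcomes, and no text tells anyone to report the smallest p-value. With only a t-test and its rank analogue the rate is 5.4% to 6.0%. Statisticians are also to be blinded to group, though picking a small p-value does not require knowing the arm labels.

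A reader might also infer three stronger points that the documents do not support:

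- That those supervising conduct know the allocations. Section 2.2 says that participants, care providers and the intervention team cannot be blinded. The blinding status of the supervising investigator is not stated.
- That "Only data validated as accurate shall constitute part of the final analysis" conflicts with intention to treat. It follows an instruction to go back to the original questionnaires when an anomaly appears, and reads as source verification. Analysing participants as randomised does not require keeping values shown to be wrong.
- That the choice for secondary outcomes, "similar mixed-effects models or simpler comparative methods, depending on the nature and timing of the data collection", is a choice driven by results. It depends on features of collection that Table 1 fixes in advance; some scales, for example, are collected only at baseline.

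**Conclusion.** The point holds for two sentences in section 3. Changing the randomisation schedule is not a remedy for data-collection or follow-up faults, and it leaves open a route for post-allocation information to reach later assignments. Its effect cannot be bounded, because the protocol does not say who would make the change or how.

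The sentence on methods, taken as written, contradicts the model named in section 2.11 and can inflate the 0.05 level. The figure of about 10-11% against about 5% is an illustrative worst case. It assumes correlations of 0.3 to 0.7, normal data, four eligible analyses and consistent reporting of the smallest p-value. It is not a forecast for this trial. The argument also takes the mixed-model sentence, which opens by referring to the main trial, as describing this trial's primary analysis.

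It would go too far to conclude that the trial could not be defended as a randomised comparison. That would depend on whether and how these permissions were used.

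**What to change.** In section 3:

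1. Delete the option to modify the randomisation schedule. Alternatively, restrict it to documented errors of the allocation system, handled by the independent sequence holder. State that failures in data collection or follow-up are met by retraining and recorded protocol deviations.
2. Replace the sentence on choosing methods with a statement that the analysis methods are fixed before any arm-level look at outcomes, and that any later change is reported as post hoc. If the timing phrase was a slip, this also corrects it.

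The cost is an edit to two sentences, passed through the protocol's own amendment route. Sample size, visits and procedures do not change.

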## Dissemination plans

4

The research team will prepare a summary of the RCT findings and distribute it via email to participants who indicated interest in receiving study results on their informed consent forms. The findings will be disseminated through publication in peer-reviewed journals and presentations at national and international conferences. Additionally, the results will be made available to other hospitals upon request for dissemination among their clinical staff. Study data will also be shared upon reasonable request, in accordance with ethical and data-sharing guidelines (39, 40).

## Discussion

5

Stroke is an acute disease that arises from the rupture or obstruction of brain vessels, which typically manifests as sudden neurological dysfunction such as limb numbness and disturbance of speech (4). Stroke has a high death incidence as well as long-standing disability (1, 2). According to the Global Burden of Disease Study 2019, stroke accounted for approximately 6.55 million deaths worldwide in that year, with about 101 million people living with the condition and a total of 143 million DALYs lost (2). While patients living through strokes of mild as well as moderate intensities document high rates of survival, they still register various intensities of functional dysfunction that may significantly impact their quality of lives dramatically (41–43). Additionally, provision of long-standing care as well as rehabilitation of such patients presents significant economic as well as psychological strains on patients’ relatives as well as on themselves, who may develop psychological as well as health conditions of their own (7, 8). Historically, the care and rehabilitation of stroke survivors have been delivered primarily through specialized health centers, a model that imposes substantial economic burdens and limits both the continuity and frequency of care. Physical rehabilitation has long prevailed over such interventions, which tends to forget the psychological well-being as well as the behavioral adjustment of patients. Correspondingly, there has long existed a need to devise new, patient-centered stroke interventions, as well as the development of LLMs presents a tenable alternative to meet such a need.

The AI-HEALS has the aim of enhancing stroke care through the use of artificial intelligence and mobile health technologies. It offers personalized health education as well as behavior change support to stroke patients and their families. Key system functions include knowledge-based question-answering services, health indicator monitoring, and personalized educational content and support tailored to the specific needs of stroke patients and their caregivers. Additionally, AI-HEALS enables care providers to monitor clients’ real-time system usage via a backend platform, facilitating the assessment of educational needs and the utilization of the intervention plan, thereby ensuring its effective implementation. Pilot studies have already indicated the tremendous promise of mobile technologies of health to deliver improved clinical outcomes when applied to stroke care. Through the support of large language models, AI-HEALS still promises to attain improved control of symptomatic improvement as well as improved recovery among patients that have mild to moderate stroke.

Based on this, this project will conduct a single-blind RCT to evaluate the effectiveness and acceptability of the AI-HEALS system in patients with mild to moderate stroke. Its primary objective will be to establish changes to patients’ blood glucose, blood pressure, and lipid profiles as a consequence of the intervention. Its secondary endpoints will include changes to perceived risk of stroke recurrence, physical health indicators such as hospital readmission rates, BMI, psychological and behavioral endpoints related to self-management of health plans, family involvement, as well as quality of life broadly. These endpoints will be examined using a combination of quantitative methods, such as standardized questionnaires and physiological measurements, and qualitative interviews. Due to the complex behavior and medical conditions involved when experiencing mild to moderate stroke, AI-HEALS has significant potentials of enhancing patient engagement as well as enhancing treatment guideline adherence.

In spite of the salutary possibilities of the planned intervention, there are certain limitations that must be recognized. First, the results may be limited in terms of generalizability as a consequence of the inclusion criterion, which aims at targeting a certain subgroup of the population that possesses specific clinical attributes. For instance, this research concentrates on patients suffering from mild to moderate stroke that are capable of utilizing digital health interventions, which may leave out patients that possess poor health literacy or have had little experience with technology. Secondly, while the research is anticipated to provide insightful knowledge on the effectiveness of the AI-HEALS system, there may be limitations in accounting for numerous external variables that impact patients’ perceptions about recurrence risk. Triggers from the environment, socioeconomic position, and accessibility to the services of delivering health, are all significant variables that may influence outcomes but cannot easily be controlled within real-world conditions. As a way of handling this, the study incorporates the demographic and the clinical covariates into the analyses of the study in an attempt to account for such influences, although there may still remain residual confounding that may impact the results. Finally, despite planning rigorous monitoring procedures designed to ensure data quality, there may still remain relevant issues such as participant dropouts as well as missing data that may still remain a threat to the validity of the results. The research team intends utilizing multiple imputations techniques as a way of overcoming such challenges; however, the possible bias that might arise from missing data must still remain carefully considered when interpreting the results.
